### Data Collection

At baseline, demographic details and data on physical and mental health outcomes will be collected by reviewing clinical records and by participants completing study instruments at recruitment (baseline) and 3 months post intervention. Baseline and follow-up data will be collected on the following:

Mental disorders, using Primary Care Evaluation of Mental Disorders/Patient Health Questionnaire [75].Substance use disorders (Alcohol, Smoking, Substance Involvement Screening Test) [76].General health status (SF-12) [77].Chronic illness and general medical morbidity (ie, clinical records review using a structured instrument previously developed by our group for morbidity surveys among problem drug users attending general practice [78].)Cardiometabolic risk, using body composition, blood pressure, and blood samples.

### Qualitative Evaluation

To explore study participants’ experience of the intervention, 6 to 8 health care professionals in participating practices and 6 to 8 patients will be interviewed in depth on the question *your experience of and satisfaction with the complex intervention, how can primary/secondary care work collaboratively to enhance physical health for patients with FEP*. Interviews will be conducted with a semistructured questionnaire (with open questions), in person or by telephone, as preferred by the participant. The conversation will be recorded digitally, and answers to the structured questions will be recorded. Each interview will be transcribed verbatim, following which the transcript will be reviewed by the researchers for accuracy.

### Data Analysis

At baseline and follow-up, descriptive statistics will be estimated with regard to key feasibility variables, that is, as follows:

Practice recruitment rate—percentage of invited practices who express an interest in participating.Patient recruitment rate—percentage of invited patients who participate.Prevalence of cardiovascular disease, diabetes, and tobacco and substance use.Practice/patient retention rates.

The IBM SPSS version 20 statistical package will be used for statistical analysis.

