### Approach to Sampling and Recruitment

The clinical lead in each of Ireland’s mental health service catchment areas will be invited to participate, and expressions of interest will be sought to participate in this feasibility study. From these expressions of interest, one urban and one rural service will be identified.

At both sites, all general practices will be eligible to participate in the study. From those who express an interest in participating, 4 practices will be selected using stratified sampling, to be representative in terms of practice size and location. Sampled GPs will be contacted about their participation, given further information on the study (eg, what their involvement will entail), and consulted about patient recruitment. The research team will telephone those not replying. Each practice will be visited by the principal investigator/lead researcher and provided with information about the research program.

At each participating practice, all patients who have been diagnosed with *FEP* in the preceding 4 years will be identified from clinical records (at the general practice or at the mental health service) and invited to participate in the study. Potential participants will be given written information on the study. Those interested in participating will be invited to meet a researcher who will be at the practice during the recruitment period. At this meeting, interested patients will be given further information on the study and will have an opportunity to ask the researcher questions. If they consent to participate, patients will be asked to sign a consent form. In total, 8 participants will be selected to participate from each practice (see Figure 2).

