### Sample Size

Semistructured interviews will be conducted with 16 health care professionals working in mental health services (n=16) to inform the *complex intervention*. Although it is difficult to predict the number of participants required to reach data saturation, our previous qualitative work [72,73] has indicated that 12 to 16 verbatim are required.

The goal of this feasibility study is to estimate rates of recruitment, consent, retention and response, methodological procedures, and issues. In addition, estimation of the parameters of likely primary outcome measures would allow the sample size of a definitive trial to be determined. With an average of 2 patients presenting to a GP with an FEP each year [74], that is, 8 per 4 years, and 8 practices in total across the 2 sites, we consider the sample size will be sufficient to estimate the actual recruitment and retention rates for a sample of patients recruited in primary care and provide data on acceptability of study processes and outcome measures which will inform a future definitive trial.

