### Ethical Considerations

Ethical considerations and safeguards include the following:

Informed consent and consenting capacity: all potential participants (GPs and patients) will be given written information on the study and the model of care being proposed and will be asked to provide written consent that they are happy to participate and that nonparticipation will not compromise their usual care. Participation in the study will be on a voluntary basis. No inducements to participate will be offered.Confidentiality: Any data/personal details that could potentially reveal the identity of individuals will be removed. Only anonymized, deidentified information will leave the practice of origin. To allow follow-up, an alphanumeric code will be assigned to each participant’s data; a database will be maintained on a password-protected database. The list will be kept separately from patient data but will indicate the medical record number of each participant and the alphanumeric code. All research data will be stored on a password-protected desktop computer at the host organization. Study participants will be invited to give permission to have their name, address, and contact details held by the research team to facilitate their receiving a synopsis of the study findings on publication and to be contacted for follow-up data collection. All data will be stored securely at the host institution.Clinical governance does no harm: it is possible that participating in the study may raise health-related issues for participants and may identify a health issue that requires clinical intervention. Therefore, all participants will be advised to speak with their doctor if participating in the study has raised any such issues. Furthermore, only patients who health care professionals deem able to participate will be asked to take part.General Data Protection Regulation (GDPR): GDPR compliance will be adhered to in terms of the following:Data privacy rights—participants will have the right to request information about their data throughout the research process.Transfer of data—participants will be informed about the circumstances under which their data may be transferred and safety measures which will be taken to protect the data (eg, data are encoded).Retention of data—patients will be informed how long their data will be stored.

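### The practice recruitment rate stops at expression of interest, so it cannot fall when a selected practice declines or never replies

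*Protocol article*

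**What the plan says.** The Data Analysis section lists two recruitment rates next to each other. The first, the practice recruitment rate, is the "percentage of invited practices who express an interest in participating". The second is "Patient recruitment rate—percentage of invited patients who participate". Practice and patient retention rates are also listed, without a definition.

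Approach to Sampling and Recruitment gives the order of events for practices. Interest comes first. Then: "From those who express an interest in participating, 4 practices will be selected using stratified sampling". This applies at each of two sites, so 8 practices in total. After selection comes the approach about taking part: "Sampled GPs will be contacted about their participation, given further information on the study (eg, what their involvement will entail"). The next sentence reads "The research team will telephone those not replying". Under Ethical Considerations, "all potential participants (GPs and patients) will be given written information on the study and the model of care being proposed", and written consent is then sought.

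The Sample Size section states the purpose: "The goal of this feasibility study is to estimate rates of recruitment, consent, retention and response, methodological procedures, and issues".

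**The concern.** A practice that expresses an interest has not yet been told what involvement entails, has not been selected and has not consented. The article's practice recruitment rate is settled at that point. A practice that is later selected and then declines, or never answers, still counts as recruited. The patient rate has the same label but counts actual participation, so the two rates measure different stages.

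This matters because estimating recruitment is the stated goal, and the Conclusions say the study will supply design parameters for a future randomised trial. Anyone planning that trial who took the practice rate at face value would approach too few practices if some drop out between interest and joining.

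**Working it through.** No figure in the article depends on this definition, so there is nothing to reproduce beyond the design count: 2 sites × 4 practices = 8. The check is one of logic, followed by illustrative proportions.

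**Order of the stages.** Invited → interested → selected and approached → joined (consented and started). Each group is contained in the one before.

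- Rate as stated = interested / invited.
- Practice uptake, u = joined / selected and approached.
- Planning yield = (interested / invited) × u. This is the share of invited practices that could be enrolled if unselected interested practices behaved like selected ones (an assumption).

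Losing a selected practice changes neither term of the stated rate. It changes only u. Read as a recruitment rate, the stated figure is too high by a factor 1/u, and the number of practices to approach is understated by the fraction 1 − u. At u = 1 both errors vanish.

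**Illustration.** The numbers invited and interested are assumptions, because the article gives neither. Eight practices are selected, and 8, 6 or 4 of them join.

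| Invited | Interested | Rate as stated | Rate × u if 8 / 6 / 4 join | Joined/invited if 8 / 6 / 4 join |
|---|---|---|---|---|
| 20 | 10 | 50% | 50 / 37.5 / 25% | 40 / 30 / 20% |
| 20 | 16 | 80% | 80 / 60 / 40% | 40 / 30 / 20% |
| 40 | 10 | 25% | 25 / 18.8 / 12.5% | 20 / 15 / 10% |
| 40 | 16 | 40% | 40 / 30 / 20% | 20 / 15 / 10% |
| 80 | 10 | 12.5% | 12.5 / 9.4 / 6.25% | 10 / 7.5 / 5% |
| 80 | 16 | 20% | 20 / 15 / 10% | 10 / 7.5 / 5% |

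Two things follow. The stated rate is the same in each row however many practices join. Joined/invited is the same whether 10 or 16 practices were interested, because the design takes only 8, so it cannot reflect willingness either.

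**Effect on planning, one row.** With 40 invited, 16 interested and 6 of 8 joining, the stated rate is 16/40 = 40% and the yield is 0.40 × 0.75 = 30%. To enrol 8 practices, the first implies approaching 8/0.40 = 20. The second implies 8/0.30 = 26.7, so 27.

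**Precision of u** (exact Clopper-Pearson 95% intervals): 8/8 = 100% (63 to 100%); 6/8 = 75% (35 to 97%); 4/8 = 50% (16 to 84%). Holding the 40% interest rate fixed, the yield at 6/8 would range from 0.40 × 0.349 = 14% to 0.40 × 0.968 = 39%, before any uncertainty in the interest rate itself.

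**The case against.** The best defence is that interest among invited practices is a sensible measure here. It is the one practice-level proportion that the cap does not limit, and its definition is printed beside its label. That stands as a reason to keep the measure under another name. It does not make it a recruitment rate.

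A second defence is that the information may be captured elsewhere. Consent is among the rates named in the study goal, GPs give written consent, and the recruitment diagram, which is not shown, would ordinarily carry counts by stage. A reader might infer that the study loses all trace of selected practices that fail to join, and the documents do not support that. But nothing in the text defines a practice uptake rate. Retention is undefined and is ordinarily counted from enrolment, so it cannot be assumed to cover the gap.

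Third, the Sample Size section's claim of sufficiency concerns patients, whose rate is defined by participation. That is fair, but the goal is worded generally and the practice rate is listed as a key feasibility variable.

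Fourth, telephoning non-repliers is a routine reminder step. It shows that silence after selection is foreseen. It does not show that refusals are expected, and the article describes no replacement procedure.

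**Conclusion.** The point holds. The stated practice recruitment rate measures interest, differs in kind from its companion patient rate and cannot register loss between selection and joining. It overstates practice uptake whenever such loss occurs, and the direction of the error is certain.

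Its size is not known. A reader might infer a definite bias, for example a 20 to 27% understatement of the number of practices to approach. That follows only if 10 or 11 must be approached to obtain 8 (1 − 8/10 = 20%; 1 − 8/11 = 27%), and the documents give no such counts. If every selected practice joins, the error is zero. Nor is the whole gap between interested and joined practices refusal, because part of it is the limit of four per site.

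A reader might also count the absence of a rate for the mental health services as a fault. The article makes no incorrect statement there, and such detail can be left to the full protocol.

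The consequence is confined to a descriptive feasibility measure. No sample size or test in the article depends on it.

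**What to change.** 1. Rename the present measure *expression-of-interest rate*: interested practices divided by invited practices.
2. Define the *practice recruitment rate* as practices that consent and start, divided by practices selected and approached. Count any replacement practice in the denominator, and give an exact 95% confidence interval.
3. Do not use joined practices over all invited practices, since the limit of 8 fixes its ceiling by design.
4. If the product of the two rates is reported for planning a later trial, report its uncertainty with it.

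The cost is one redefinition and a count of practices at each stage, which a recruitment diagram would ordinarily need anyway. Design and sample size do not change. The drawback is that the recruitment figure may be less favourable, and with about 8 practices it will be imprecise.

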### Qualitative Data Analysis

Thematic analysis will be used to analyze qualitative data. This approach has many benefits for studies such as this which are interpretive in nature, as it is a “method for identifying, analyzing and reporting patterns (themes) within data” [79]. The process of thematic analysis is concerned with the basic to advanced encoding of data. The codes are subsequently developed to themes. This flexible approach can also be seen in how themes identified at one level can help the researcher describe their observations and at a more advanced level allow the researcher to interpret aspects of the phenomenon under study [79]. The qualitative research software NVivo version 8 will be used to facilitate the coding of these data. The analysis will follow a *5-Step Analysis* approach whereby data are reviewed, examined, coded, and themes generated and defined [79]. To achieve validity in the coding/analysis of data, 2 reviewers will code data independently and inter-rater reliability measures will be computed based on this coding. Coding consistency will be maintained throughout the coding process and will be reviewed by regular meetings between researchers and the principal investigator. The findings will be compared with other study findings (validity and credibility). The researchers will present the findings to participants to determine if the study findings reflect their experience of the topic under study (member checking). Illustrative quotes will be used to emphasize points made by the participants **.**

### Ethical Considerations

Ethical considerations and safeguards include the following:

Informed consent and consenting capacity: all potential participants (GPs and patients) will be given written information on the study and the model of care being proposed and will be asked to provide written consent that they are happy to participate and that nonparticipation will not compromise their usual care. Participation in the study will be on a voluntary basis. No inducements to participate will be offered.Confidentiality: Any data/personal details that could potentially reveal the identity of individuals will be removed. Only anonymized, deidentified information will leave the practice of origin. To allow follow-up, an alphanumeric code will be assigned to each participant’s data; a database will be maintained on a password-protected database. The list will be kept separately from patient data but will indicate the medical record number of each participant and the alphanumeric code. All research data will be stored on a password-protected desktop computer at the host organization. Study participants will be invited to give permission to have their name, address, and contact details held by the research team to facilitate their receiving a synopsis of the study findings on publication and to be contacted for follow-up data collection. All data will be stored securely at the host institution.Clinical governance does no harm: it is possible that participating in the study may raise health-related issues for participants and may identify a health issue that requires clinical intervention. Therefore, all participants will be advised to speak with their doctor if participating in the study has raised any such issues. Furthermore, only patients who health care professionals deem able to participate will be asked to take part.General Data Protection Regulation (GDPR): GDPR compliance will be adhered to in terms of the following:Data privacy rights—participants will have the right to request information about their data throughout the research process.Transfer of data—participants will be informed about the circumstances under which their data may be transferred and safety measures which will be taken to protect the data (eg, data are encoded).Retention of data—patients will be informed how long their data will be stored.

Application will be made to the Health Service Executive, Irish College of General Practitioners (GPs) and University College Dublin Research Ethics Committees.

## Results

The study findings have the potential to provide important information on how key workers might enhance collaboration between primary and secondary care to improve outcomes for patients with FEP.

## Discussion

### Strengths and Limitations

This study is the first study to examine how key workers might enhance collaboration between primary and secondary care to improve outcomes for patients with FEP. It will provide important information to enhance scientific understanding of the role of key workers in improving health outcomes for patients with FEP. It will provide key information to inform health policy and service development in Ireland and internationally. However, it may be difficult to extrapolate these results among a high-risk population because of the specificity of the symptomatology in the early phases. This study has the potential to make an important impact on patient care and will provide high-quality evidence to help inform health care professionals on the importance of key workers for FEP patients. The intervention is scalable and, therefore, if found to be feasible and acceptable, it can be readily implemented elsewhere and used to guide policy and service development internationally.

Possible limitations of the study include potential issues of bias and lack of generalizability that may arise from the recruitment process, owing to the likelihood that health care professionals who are more interested in research and innovation will choose to participate. As qualitative data analysis is open to interpretation, there are also potential issues of bias that may arise from data analysis. The use of multiple researchers during the qualitative analysis phase will attempt to reduce this possibility. Despite these potential limitations, this study will provide important information regarding the role of key workers in improving collaboration between primary and secondary care to improve health outcomes for patients with FEP.

### Conclusions

At the end of this study, the feasibility of a clinical intervention, informed by international best practices and local barriers, will be evaluated among a high-risk population. This feasibility study will inform clinical practice by providing initial indications as to how key workers might enhance collaboration between primary and secondary care to improve outcomes for patients with FEP. It will also inform future research on the topic by providing key parameters for the design of a future randomized controlled trial.

## Abbreviations

EIP: Early Intervention in Psychosis
EISs: early intervention services
FEP: First Episode Psychosis
GDPR: General Data Protection Regulation
GP: General Practitioner
